## 10. STATISTICAL ANALYSIS

### 10.1 Primary study parameters

For analysis of the results, the groups will be stratified for gender and the female patient group will be balanced for pre- and post-menopausal. Data analysis will be performed using SPSS. The primary analysis will be to assess difference between the intervention and the control groups in the sUTI rate and other adverse effects. Descriptive statistics will be used to describe baseline characteristics of participating patients in both groups. Binomial or categorical outcome measures will be analyzed using Chi-square tests and quantitative outcome variables by t-tests or Mann-Whitney U tests. Two-sided p values are calculated.

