### 3.2 Randomisation

Randomisation is done by the tool ALEA (meaning ‘dice’ in Latin), according to the regulations of the Erasmus MC. ALEA is developed for randomisation and guarantees concealed allocation. The intervention and control group will be stratified for the participating centres, neurogenic and non-neurogenic causes for catheterisation, age (16–17 years vs  $\geq 18$  years and  $< 50$  years vs.  $\geq 50$  years old), gender, and the female patient group will be balanced for premenopausal and postmenopausal status. On randomisation, patients will be allocated a unique study subject number in chronologically ascending order for every study site, starting with 1 (e.g., Erasmus MC: EMC001). They will be randomized to the intervention arm (reusable catheter) or control arm (single use catheter). There is no prespecified list on randomisation, but each combination of stratification factors will form a combination. Within each combination, ALEA will randomly assign a study arm. The rationale for this approach is that it will maximise the probability of assigning a new participant in

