### 3.3.3 Decision Rule

This trial is designed to address a single primary outcome. Non-inferiority is claimed if the primary null hypothesis is rejected on the significance level (alpha) of 0.025 (one-sided). That is, if the upper-limit of the two-sided 95% confidence interval for the treatment difference is less than 7%.

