### 4.2 Baseline Patient Characteristics

The patient demographics and baseline characteristics to be summarised include age in years, BMI, sex, menopausal status, race, comorbidities (COPD, DM2, hypertension, cardiovascular disease), underlying cause of catheterization (e.g., NLUTD vs non-NLUTD), spontaneous miction, hand function, years of CIC experience, CIC frequency, Antibiotic prophylaxis, bladder irrigation, intradetrusor botulinum toxin A, self-reported UTI in previous 6 months before trial.

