## 6.1.2 Primary Analysis

For the primary outcome, the incidence rate in each group is the total number of UTIs divided by the total follow-up time, reported with 95% confidence intervals calculated using bootstrap procedure. The absolute difference between groups will be calculated and reported with a 95% bootstrap confidence interval. Non-inferiority will be concluded if the upper limit of the CI is below the non-inferiority margin of 7%. The incidence rate ratio (IRR) with a 95% CI will be estimated in both arms using a poisson or negative binomial regression model (in case there is overdispersion of the data). All analyses will be conducted using R version 4.2.1 (R Foundation for Statistical Analysis, Vienna, Austria).

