## 6.2 Methods for secondary outcomes

### 6.2.1 Methods for outcomes of questionnaires (ISCQ, InCaSaQ, EQ-5D-5L, SF-Qualiveen, PGI-I).

#### 6.2.1.1 Descriptive Statistics

Continuous variables will be described using means and standard deviations. Categorical variables will be described using frequency (n) and percentages (%).

Linear mixed models (LMMs) will be used to assess longitudinal trajectories of the PROs between the two treatment arms. The models will include fixed effects for treatment group, time, and the interaction between time and treatment group. Since all questionnaires are collected at the same follow-up scheme, time will be used as a categorical variable (9). To account for within-subject correlation, a random intercept will be included for each patient. Adjustment for confounders is deemed unnecessary, as stratified randomization is applied. Baseline, as well as the scores at 6 weeks, 26 weeks and 52 weeks are included in the model. Longitudinal linear mixed model analyses correct for missing responses at random (9). The interaction between “time x treatment arm” is included in the model as interaction to assess whether the treatment arm had different effects on the outcomes of the questionnaires at different points in time (9).

A post hoc subgroup analysis is conducted to examine outcomes by gender (male vs. female), age

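### The primary non-inferiority analysis is a crude rate difference that leaves out the randomisation factors and the recorded UTI history, so precision is forgone; separately, the SAP's reason for not adjusting the questionnaire models is mistaken

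*Combined protocol and SAP*

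**What the plan says.** **Primary analysis (SAP 6.1.2).** "the incidence rate in each group is the total number of UTIs divided by the total follow-up time". For the contrast, "The absolute difference between groups will be calculated and reported with a 95% bootstrap confidence interval". Under SAP 3.3.3, non-inferiority is claimed "if the upper-limit of the two-sided 95% confidence interval for the treatment difference is less than 7" percent. An incidence rate ratio is also to be estimated "using a poisson or negative binomial regression model", but it plays no part in the decision. No covariate or stratum is named for either quantity, and no reason is given for leaving them out.

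**Allocation (SAP 3.1 and 3.2).** SAP 3.1 calls the method minimisation. SAP 3.2 says "The intervention and control group will be stratified for the participating centres, neurogenic and non-neurogenic causes for catheterisation", and adds age, gender and, among women, menopausal status.

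**Baseline data (SAP 4.2).** The listed characteristics include "self-reported UTI in previous 6 months before trial". They are summarised by arm, and clinically important imbalance is to be noted. No analysis uses the UTI history.

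**Protocol 10.1.** "For analysis of the results, the groups will be stratified for gender", with women balanced by menopausal status. SAP 6.1.2 contains nothing that corresponds.

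**Questionnaires (SAP 6.2.1.1).** The linear mixed models have arm, time and their interaction as fixed effects and a random intercept per patient. The stated reason for going no further is "Adjustment for confounders is deemed unnecessary, as stratified randomization is applied". This sentence appears only here, under the secondary outcomes.

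**The concern.** Two things look wrong.

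First, when allocation is forced to balance on factors that predict UTI, the true sampling variation of the treatment difference is smaller than under simple randomisation. An analysis that ignores those factors, including a bootstrap that resamples patients without regard to them, does not credit that balance, so its interval tends to be too wide. The UTI history is a different case because it is not a randomisation factor. The crude interval is honest about chance imbalance in it, but wider than it needs to be, since a direct indicator of each patient's tendency to UTI has already been recorded.

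Second, SAP 6.2.1.1 treats balanced allocation as a reason not to adjust. Balance removes the need to adjust for confounding. It does not remove the gain in precision, and it makes the unadjusted standard error too large.

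At stake is the width of the one interval that decides the trial. Timing also matters. The trial is unblinded (protocol 8.2), so if prior UTI turned out unbalanced, an adjustment chosen at that stage would look data-driven. It carries weight only if it is prespecified.

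**Working it through.** **1. Reproduce the plan's figure.** Inputs from SAP 6.3 and protocol 4.4: SD 0.21, one-sided alpha 0.025, power 0.80, rates 0.13 and 0.14 per month, margin set at half the mean rate.

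- Half the mean of 0.13 and 0.14 = 0.0675, which the plan prints as 7%.
- n = 2 × SD² × (z0.975 + z0.80)² / d² = 2 × 0.0441 × 7.849 / 0.0675² = 151.9, so 152 per arm. This matches the plan.
- With d = 0.07 the same formula gives 141.3, so 142, which does not match.

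The plan's 152 therefore rests on a raw, unadjusted SD, a true difference of zero and the unrounded margin. The planned power never counted on adjustment.

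**2. Power with and without adjustment.** Take 154 evaluable per arm (193 × 0.80 = 154.4). Let R² be the share of outcome variance that the covariates explain. The documents give no value, so R² is an assumption throughout.

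- SE = 0.21 × √(2(1 − R²)/154)
- Power = Φ((margin − true difference)/SE − 1.96)

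Unadjusted, SE = 0.21 × √(2/154) = 0.0239. On the plan's assumptions, 0.0675/0.0239 − 1.96 = 0.86 and Φ = 80.5%. With a true difference of 0.01 and margin 0.07, 0.06/0.0239 − 1.96 = 0.55 and Φ = 70.8%.

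| R² (assumed) | 95% CI half-width | Power: difference 0, margin 0.0675 | Power: difference 0.01, margin 0.07 | n per arm for 80% (difference 0, margin 0.0675) |
|---|---|---|---|---|
| 0 | 0.0469 | 80.5% | 70.8% | 152 |
| 0.05 | 0.0457 | 82.5% | 73.0% | 145 |
| 0.10 | 0.0445 | 84.5% | 75.3% | 137 |
| 0.20 | 0.0420 | 88.4% | 80.0% | 122 |

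The factor (1 − R²) is exact for linear adjustment. For a difference standardised from a count model it is an approximation.

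**3. What R² might prior UTI alone give?** Assume gamma-Poisson counts with mean 0.135 per month, a six-month baseline count recalled exactly, twelve months of follow-up, and correlation ρ between a patient's underlying rates in the two periods. With between-patient variance τ² = SD² − 0.135/12:

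R² = ρ²τ⁴ / [(τ² + 0.135/6)(τ² + 0.135/12)]

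- SD 0.21: τ² = 0.03285, and R² = 0.44, 0.22 and 0.11 for ρ = 1, 0.7 and 0.5.
- SD 0.18: τ² = 0.02115, and R² = 0.32, 0.15 and 0.08.

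The top values need stable rates and perfect recall, so they are a ceiling. Self-report, set against a trial outcome that requires a positive test (SAP 5.2), would pull R² down, and so would recording the history as yes/no.

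**4. Planned use of each item.** Centre and menopausal status: allocation and description only. Gender and neurogenic cause: allocation, plus a questionnaire subgroup model that the SAP itself labels post hoc. Age: the same, but with a different cut-off (65 in the subgroup model; 18 and 50 at allocation). Prior UTI: description only. None of them enters the primary estimate.

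**The case against.** The strongest reply is that this is a preference about efficiency. The crude comparison is valid under randomisation. An interval that is somewhat too wide makes non-inferiority harder to claim, not easier. Chance imbalance in prior UTI is part of the sampling error that the interval expresses. The sample size was set for an unadjusted analysis, so nothing that was planned is lost. All of this stands, and it limits the finding to forgone precision.

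Three stronger readings are tempting, and the documents do not support them.

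- *That the sentence in SAP 6.2.1.1 is the reason for the crude primary analysis.* It governs the questionnaire models only. SAP 6.1.2 offers no reason at all.
- *That omitting covariates leaves the trial at about 71% power.* The 70.8% comes from adding a true difference of 0.01, which the sample size formula does not contain. That is a separate question. It also counts only 154 per arm, whereas the estimator uses all follow-up time. If all 193 contributed fully, the same formula gives 80.1%, an upper bound because partial follow-up adds variance. With the plan's two SDs of 0.18 and 0.21, the figures are 76.8% at 154 and 85.4% at 193.
- *That a large gain is assured.* Every R² is assumed, and SAP 4.2 does not say whether the UTI history is a count or yes/no.

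Two further qualifications are fair. Protocol 10.1 is weak support for an adjusted estimate: its wording echoes the randomisation section and the tests it names are unadjusted. It shows an inconsistency to resolve, not a clear commitment. And the SAP does model gender, age group and cause for the questionnaires, though only in the post hoc subgroup model.

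**Conclusion.** The point holds as forgone precision. The deciding interval in SAP 6.1.2 ignores both the allocation factors and the UTI history, without a stated reason and out of step with protocol 10.1. The rationale in SAP 6.2.1.1 is wrong in itself and should go.

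The size cannot be fixed from the documents. With 154 per arm and a common SD of 0.21, adjustment adds about 2, 4 or 8 points of power for R² of 0.05, 0.10 or 0.20 on the plan's own assumptions, and about 2, 4.5 or 9 points with a true difference of 0.01 and margin 0.07. There is no bias, and under its own assumptions the crude analysis meets the planned 80%. The change is worth making because it costs almost nothing and must be settled before outcomes are compared by arm.

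**What to change.** **SAP 6.1.2.** Make the primary estimate an absolute difference in monthly UTI rate, standardised over the analysed patients from a negative binomial model. The model has log follow-up time as offset and contains arm, the randomisation factors (with a stated rule for pooling small centres) and UTI in the previous six months in the form recorded, count or yes/no. Obtain the 95% interval by resampling patients within arm and refitting, and compare its upper limit with the margin. Keep the crude difference as a sensitivity analysis. If the sponsor prefers the crude estimate as primary, the SAP should say why.

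**Protocol 10.1.** Reconcile the statement on gender and menopausal status with SAP 6.1.2, so that both name the same factors.

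**SAP 6.2.1.1.** Delete the sentence on confounders and add the randomisation factors to the mixed models as fixed effects.

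**Optional.** Constrain the arms to a common baseline mean in the mixed models, since baseline precedes treatment, and adjust QALYs for baseline EQ-5D in the cost-effectiveness analysis. Neither is needed to settle this point.

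**Cost.** SAP wording and a little programming; a Poisson or negative binomial model is already planned. No new data are needed. The downside is that the primary estimate becomes model-based, which reporting the crude difference beside it largely answers.

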# STATISTICAL ANALYSIS PLAN for COMPaRE-trial

---

(<65 vs. ≥65 years), and the ethology of lower urinary tract symptoms (LUTS) (neurogenic vs. non-neurogenic origin), using linear mixed-effects models. The model will include fixed effects for treatment arm, gender, age group, and LUTS ethology, as well as interaction terms between the treatment arm and each subgroup variable. Holm's method for multiple comparisons correction will be applied to adjust p-values. The age cut-off is determined based on the median age of the study population.

To facilitate interpretation of changes in the questionnaire scores, effect sizes will be calculated with the use of Cohen's D test. An effect size of 0.3 or less is considered small, more than 0.3 to 0.8 moderate, and more than 0.8 large (10).

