| Week 42                  | Telephone call   | The use of both types of catheters will be evaluated, patients will be asked for adverse events via standardized questions in Gemstracker/LimeSurvey and possible risen questions will be answered.                                                                                                                                      |                                                                                                                                                                                                                                                                      |
| Week 52, endpoint | Clinical visit 2 | 
After completing the twelve months of follow up, patients will be asked one last time for adverse events via standardized questions in Gemstracker/Limesurvey. Additionally the trial will be evaluated.
 
- Urinary samples will be obtained for testing
                                                                    | 
 
- EQ-5D-5L
 
- SF-Qualiveen
 
- ISC-Q
 
- IncasaQ
 
- iMCQ
 
- iPCQ
 
- PGI-I
 
- Two opinion questions about the environmental and financial burden of catheters
 
 |

All questionnaires will be sent to the patients by email prior to the contact moment by Limesurvey/Gemstracker.

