#### 8.1.2 Secondary study parameters/endpoints

Secondary outcome measurements are symptom specific and quality of life related questionnaires (PGI-I, EQ-5D-5L and SF-Qualiveen), the amount of urethral damage/strictures and kidney/bladder stone formation. To evaluate if urinary cultures/urinary microbiome changes if a patients is reusing a catheter, the patients will hand in catheterized urinary samples for testing at the two clinical visits.

Furthermore, economical evaluation of the cost-effectiveness of single-use versus reusable catheters will be performed in cooperation with the health economist within our project group, using the iMCQ and iPCQ questionnaires, which will be entered at week 6, week 26 and week 52. The costs of the Cliny catheter set, including the sterilizing solution, will be included in the economical evaluation. Patients perspective on ease of use and cleaning of the reusable catheters compared to the single-use catheters will be evaluated by the ISC-Q, the InCaSaQ and, for the

intervention group, also the PGI-I questionnaire. These questionnaires are developed to investigate difficulties in use, the impact of catheterization on patients and the overall acceptance in patients and will be entered at baseline, week 6, week 26 and week 52. Overall quality of life will be evaluated by the EQ-5D-5L measure method and the SF-Qualiveen and will be entered at baseline, week 6, week 26 and week 52. All used questionnaires are validated in Dutch.

Two additional questions concerning patients thoughts on environmental burden and healthcare costs will be asked at week 0 and week 52.

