### 3.3.2 Confidence Intervals and p-values

All calculated p-values will be two-sided and compared to a 5% significance level. If a p-value is less than 0.05, the corresponding treatment group difference will be denoted as statistically significant. All efficacy estimates will be presented with two-sided 95% confidence intervals. As there is only one primary null hypothesis to be tested in this trial, there will be no adjustments for multiplicity.

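### The subgroup term for the questionnaires has no time component; with week 0 among the outcomes, as the SAP describes, it understates a constant follow-up subgroup difference by about a quarter

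*Combined protocol and SAP*

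**What the plan says.** SAP 6.2.1.1 first sets out the main questionnaire model. On fixed effects: "The models will include fixed effects for treatment group, time, and the interaction between time and treatment group". On correlation: "a random intercept will be included for each patient". On the outcome data: "Baseline, as well as the scores at 6 weeks, 26 weeks and 52 weeks are included in the model". The SAP's overview of outcomes agrees, giving ISCQ, InCaSaQ, SF-Qualiveen and EQ-5D-5L four time points each.

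The same section then turns to subgroups: "A post hoc subgroup analysis is conducted to examine outcomes by gender", and also by age group and by neurogenic or non-neurogenic origin, again with linear mixed-effects models. Its terms are given as: "The model will include fixed effects for treatment arm, gender, age group, and LUTS ethology, as well as interaction terms between the treatment arm". All three factors are crossed with arm. The subgroup text mentions neither time nor an arm-by-subgroup-by-time term. It does not say whether week 0 is kept as an outcome, dropped or used as a covariate. Holm's method is to adjust the p-values.

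The week-0 score precedes treatment. Protocol section 3 says of the questionnaires: "All questionnaires will be sent to the patients by email prior to the contact moment", and randomisation takes place at the week-0 visit (protocol 11.2). The same schedule lists PGI-I only at weeks 6, 26 and 52.

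**The concern.** The clinical question is whether the effect of reusable catheters on satisfaction or quality of life differs by gender, age or cause of retention. In the main model the time-by-arm term separates the pre-treatment visit from follow-up. The subgroup model, as listed, loses that separation. Its arm-by-subgroup coefficient compares subgroups on an average over all visits, and at one of those visits the true treatment effect is zero by design.

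The null hypothesis tested is therefore that there is no arm-by-subgroup difference averaged over weeks 0, 6, 26 and 52. If one sex, or neurogenic patients, tolerated reuse less well, the reported interaction would be too small. A non-significant result could then be read as reassurance that all groups do equally well.

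**Working it through.** **Inputs from the documents.** Four occasions (weeks 0, 6, 26, 52); random intercept, hence equal correlation between visits; two-sided 5% tests (SAP 3.3.2); 386 patients and 20% dropout (SAP 6.3). The documents give no effect size, SD, within-patient correlation or power for these tests, so there is no planned figure to reproduce.

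**Assumptions.** Score SD 1; within-patient correlation ρ of 0.3, 0.5 or 0.7; a subgroup split of 50/50 (the SAP supports this for age only, where the cut-off follows the median).

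**Step 1: size of the coefficient.** With complete data and a random intercept, the arm-by-subgroup estimate is the contrast in four-visit means. Let the true interaction be 0 at week 0 and δ at each follow-up visit:

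(0 + δ + δ + δ)/4 = 0.75δ, which is 25% too small for every ρ.

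Generalised least squares gives the same 0.75 with no time terms, with time, and with time plus time-by-arm. Those terms do not involve the subgroup, so they cannot separate week 0 from follow-up in the interaction. For a difference present at week 52 only, the coefficient is (0 + 0 + 0 + δ)/4 = 0.25δ.

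**Step 2: dropout.** Suppose the 20% loss accrues linearly over 52 weeks and is monotone. The proportions observed are 1 − 0.20 × 6/52 = 0.977 at week 6, 0.90 at week 26 and 0.80 at week 52. Week 0 then gains weight, and the coefficient for a constant δ becomes 0.719δ, 0.714δ and 0.710δ at ρ = 0.3, 0.5 and 0.7. That is 28-29% too small.

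**Step 3: power.** Up to a common factor, the variances are:

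- planned term: (1 + 3ρ)/4, with expectation 0.75δ
- follow-up mean adjusted for baseline: (1 + 2ρ)/3 − ρ²
- follow-up mean minus baseline: (4/3)(1 − ρ)
- follow-up mean alone: (1 + 2ρ)/3

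Choose δ so that the comparator has 80% power at an unadjusted two-sided 5%, so its standardised effect is 1.960 + 0.842 = 2.802. The planned term's standardised effect is 2.802 × 0.75 × √(comparator variance / planned variance).

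Example, ρ = 0.5, baseline-adjusted comparator: √(0.4167/0.625) = 0.8165; 0.75 × 0.8165 = 0.612; 2.802 × 0.612 = 1.716. Power is Φ(1.716 − 1.960), about 40%.

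Power of the planned term when the comparator has 80%:

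| Comparator | ρ = 0.3 | ρ = 0.5 | ρ = 0.7 |
|---|---|---|---|
| Baseline-adjusted follow-up | 52.8% (loss 27.2) | 40.4% (loss 39.6) | 26.5% (loss 53.5) |
| Follow-up minus baseline | 83.8% (gain 3.8) | 58.3% (loss 21.7) | 32.6% (loss 47.4) |
| Follow-up alone | 60.5% (loss 19.5) | 58.3% (loss 21.7) | 56.9% (loss 23.1) |

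A simulation of 386 patients with 3,000 replicates gave ratios of 0.749, 0.750 and 0.746, and planned-term power of 52.3%, 41.1% and 26.9% where the baseline-adjusted model had about 80%.

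**Step 4: sensitivity.** Against the baseline-adjusted model, the loss is about 20 to 35 points if the reference power is 50%, and 12 to 20 points if it is 30%. At the strictest Holm step for three interactions (0.05/3 = 0.0167; the SAP does not define the family), with 80% reference power, it is 32 to 60 points. With 386 patients and a 50/50 split, 80% power for the baseline-adjusted test corresponds to an interaction of 0.32 to 0.38 SD.

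**Step 5: false positives.** With no subgroup difference at any visit, simulated rejection rates were 0.050, 0.051 and 0.050.

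**The case against.** The strongest reply is that the subgroup text is an incomplete list, not a full model formula. It names no visits, no random effect and no handling of baseline; week 0 as an outcome is carried over from the main-model paragraph. That is correct, and the point is therefore conditional on that reading. It still matters, because no other outcome set is described for these models, and supplying the main model's time and time-by-arm terms leaves the 0.75 unchanged.

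A second reply is that this is a secondary analysis labelled post hoc, for which the trial was not sized. That also stands, and it limits the importance of the point. The SAP does specify the model and a multiplicity correction, so the results will be reported as formal tests.

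A reader might go on to infer more than the documents support:

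- **That any true subgroup difference shrinks by exactly 25%.** That figure needs a constant follow-up difference and complete data. Dropout or late onset changes it.
- **That the test loses 27 to 53 points of power as a property of the plan.** The range rests on assumed correlations, a hypothetical 80% reference power, unadjusted alpha and one choice of comparator. Against a follow-up-minus-baseline contrast at ρ = 0.3, the planned term does slightly better.
- **That every questionnaire is affected.** On the protocol section 3 schedule, PGI-I has no week-0 score to dilute its estimate.

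**Conclusion.** The concern holds as a defect of a secondary analysis. Followed as written, with the outcome visits the SAP gives for its questionnaire models, the arm-by-subgroup coefficient for ISCQ, InCaSaQ, EQ-5D-5L and SF-Qualiveen answers the wrong question. The firm result is the attenuation: 25% for a difference constant over follow-up with complete data, 28-29% under the assumed linear 20% dropout, and 75% for a difference at week 52 only with complete data. The power cost can be large but is not fixed by the documents, and should be quoted only with its assumptions. The error is towards missing a subgroup difference, not towards declaring one falsely. The primary non-inferiority decision does not use this model.

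**What to change.** In SAP 6.2.1.1, state the full subgroup model:

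- **Outcomes:** scores at weeks 6, 26 and 52, with the week-0 score as a covariate. For PGI-I, use follow-up scores without a baseline covariate.
- **Fixed effects:** arm, time, the subgroup factors, arm-by-time and arm-by-subgroup. Add arm-by-subgroup-by-time if visit-specific subgroup effects are wanted.
- **Reporting:** the arm difference within each subgroup, and the interaction with its 95% CI.

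If the sponsor prefers to keep week 0 as an outcome, the subgroup effect should be read from an arm-by-subgroup-by-time contrast of follow-up against baseline, not from the two-way term.

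Protocol 8.1.2 mentions PGI-I for the intervention group and groups it with instruments completed at baseline. That should be reconciled with the section 3 schedule, since an arm comparison needs PGI-I in both arms.

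The cost is a few lines of SAP text and a changed model formula, with no new data. The small downside is that patients without a baseline score need a simple stated rule, such as mean imputation of the covariate.
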